### Outcome measures

Participants will be followed for 12 months following completion of the initial training period. During this time, falls, activity, and participation will be reported regularly. Balance confidence and functional balance and mobility will be assessed at study enrolment, immediately after the initial training period, six-months after the initial training period, and at the end of the 12 months follow-up. All data will be collected by a trained research assistant who is blinded to group allocation. Table 2 summarizes that measures that will be taken at each time point.

**Table 2 Tab2:** Summary of outcome measures and assessment time points

	Pre-training assessment	Post-training, interim and follow-up assessments	12-months follow-up period
Demographic and stroke information	✓		
Medical conditions	✓	✓	
Medications	✓	✓	
NIH-SS	✓		
CMSA	✓		
Lean-and-release test	✓		
BBS	✓	✓	
Mini-BES	✓	✓	
TUG	✓	✓	
ABC	✓	✓	
Falls reporting^a^	✓		✓
PASIPD^b^	✓		✓
SIPSO^b^	✓		✓

^a^Reported continuously throughout the 12-months follow-up period

^b^Questionnaires completed approximately every 2-months throughout the 12-months follow-up period

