#### Secondary outcomes (pre-post) – functional balance and mobility, and balance confidence

Pre-post measures will be obtained immediately before and after the initial period of training, and 6 and 12 months after the end of the initial training period. Functional balance and mobility will be assessed using the Berg balance scale (BBS [67]), the mini-Balance Evaluation Systems test (mini-BES [68]), and the ‘Timed Up & Go’ (TUG [69]). The BBS is a 14-item observational rating scale that provides a measure of functional balance. Participants will be asked to perform each of the 14 tasks, and their ability to perform each task will be rated on a scale from 0–4. The BBS shows good internal consistency (Cronbach’s α = 0.92–0.98) and good inter-rater (ICCs = 0.95–0.98), intra-rater (ICCs = 0.97), and test-retest (ICC = 0.98) reliability in the stroke population [70]. The mini-BES is a 14-item observational rating scale that assesses systems underlying balance control, including reactive balance control and dynamic stability during walking [68]. The mini-BES has good inter- (ICC = 0.96) and intra-rater reliability (ICC = 0.97) among individuals with stroke [71]. The BBS is commonly used in balance training studies and clinical settings; therefore, inclusion of this measure will allow for comparison between the proposed and previous trials. The mini-BES is a more specific measure and is less susceptible to floor and ceiling effects than the BBS [71]; thus, the mini-BES may be more likely to reveal training-related changes in reactive control and dynamic stability during walking. The TUG is a frequently-used test of functional mobility that is related to falls risk [72–74]. Participants will be seated in a 45 cm high chair with armrests, and will be instructed to rise from the chair, walk “as quickly as is safe” to a marker placed 3 m directly in front of the chair, to circle the marker, and then to return to the chair. Participants will be allowed to use the armrests to assist them with rising from the chair only if absolutely necessary. The time taken from the start command until the participant sits back in the chair will be measured. The TUG has excellent test-retest reliability among individuals with stroke (ICC = 0.95; [75]). The Activity-specific Balance Confidence (ABC) questionnaire [76] will be used to assess balance confidence during daily activities before and after training. The ABC asks participants to rate, on a scale from 0–100 %, how confident they would be performing 16 everyday tasks. The ABC shows good internal consistency (Cronbach’s α = 0.94) and test-retest reliability (ICC = 0.85) in individuals with stroke [77].

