
### Statistical analysis and sample size

Negative binomial regression will be used to compare fall rates between the two groups and logistic regression will be used to compare the proportion of fallers between the two groups. If the groups differ on prognostic factors (e.g., stroke severity) or on physical activity during the follow-up period (i.e., PASIPD scores) then multiple negative binomial/logistic regression will be used. Intent-to-treat analysis will be used; all individuals with some falls-monitoring data will be included in the analysis. Survival analysis may be considered if a large number of individuals do not complete the entire 12-month follow-up. Exploratory per-protocol analysis and/or comparison of fall rates between those who return for the ‘booster’ training sessions and those who do not may also be conducted. Repeated-measures analysis of variance, with group-by-time interaction, will be used to evaluate the effect of the interventions on secondary outcome measures (e.g., functional balance measures, balance confidence). The interaction effect will reveal if there is a greater pre- to post-training improvement in the perturbation training group compared to the control group.

The target sample size has been estimated using a formula for negative binomial regression described elsewhere [78]. Assuming a rate of falls in the control group of 1.75 per person per year [27], a reduction in rate of falling of 46 % in the perturbation training group [35], mean follow-up time of 11 months per person (i.e., some participants will be lost to follow-up before 12 months), level of significance (α) of 0.05, and power (1-β) of 0.8, we estimate that 37 participants per group will be required to show significant effects. From previous studies [32, 79], we expect that ~20 % of individuals will withdraw prior to completing the intervention. While many of these individuals will be willing to complete the 12-month falls monitoring period and could be included in intent-to-treat analysis, we conservatively assume that 20 % of individuals will withdraw from the study. Therefore, we will aim to recruit at least 46 participants per group (i.e., 92 participants total).

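### With four scheduled visits, the group-by-time interaction does not by itself test the pre- to post-training gain that the protocol says it reveals

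*Protocol article*

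**What the plan says.** The protocol article, under Statistical analysis and sample size, states: "Repeated-measures analysis of variance, with group-by-time interaction, will be used to evaluate the effect of the interventions on secondary outcome measures". It names functional balance measures and balance confidence as examples. It then interprets the test: "The interaction effect will reveal if there is a greater pre- to post-training improvement in the perturbation training group compared to the control group". The section does not say which visits make up the time factor, and it names no contrast between particular visits.

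The schedule is given in other sections. Under the pre-post secondary outcomes: "Pre-post measures will be obtained immediately before and after the initial period of training, and 6 and 12 months after the end" of initial training. The Outcome measures section agrees; these variables "will be assessed at study enrolment, immediately after the initial training period, six-months after the initial training period, and at the end" of follow-up. Trial design gives the same four occasions. The measures concerned are the Berg balance scale, the mini-BES, the Timed Up & Go and the ABC questionnaire.

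On attrition, the protocol writes: "we expect that ~20 % of individuals will withdraw prior to completing the intervention". Its intent-to-treat inclusion rule is worded for the falls data: "all individuals with some falls-monitoring data will be included in the analysis".

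**The concern.** The interpretive sentence describes a directional comparison between two time points. A group-by-time interaction over four time points is a different test: it asks whether the two mean profiles differ in shape anywhere. A significant result could come entirely from the 6- or 12-month visits, and by the protocol's own sentence it would be reported as a greater gain from training. Conversely, a real immediate gain that wears off could be missed because the test is spread over visits where little difference remains. The secondary hypothesis of greater gains in balance, mobility and confidence would then rest on a test that does not match the statement made about it.

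**Working it through.** **Inputs from the protocol.** Four visits. The recruitment target is 46 per group; with 20% withdrawal this leaves 46 × 0.8 = 36.8, about 37 per group, which is also the number the protocol requires before inflation. The protocol gives no power figure, effect size or between-visit correlation for the secondary outcomes, so there is no stated figure to reproduce on this point.

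**Assumptions.** Two-sided 5% level, compound symmetry, correlation ρ = 0.7 (varied below), and between-group differences in SD units at the pre, post, 6- and 12-month visits:
- sustained gain: 0, 0.4, 0.4, 0.4
- fading gain: 0, 0.4, 0.2, 0.1
- late divergence only: 0, 0, 0.2, 0.4

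**Formulas** (noncentral F, n per group, visit differences δj with mean δ̄, pre-to-post difference δ):
- four-visit interaction: λ = (n/2) Σ(δj − δ̄)² / (1 − ρ), on 3 and 3(2n − 2) df
- pre-to-post change contrast: λ = (n/2) δ² / [2(1 − ρ)], on 1 and 2n − 2 df
- baseline-adjusted comparison at the post visit: λ = (n/2) δ² / (1 − ρ²), on 1 and 2n − 3 df

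**Numbers at n = 37, ρ = 0.7** (n/2 = 18.5):
- Sustained: Σ = 0.09 + 3 × 0.01 = 0.12; interaction λ = 18.5 × 0.12/0.3 = 7.40.
- Fading: Σ = 0.0875; interaction λ = 18.5 × 0.0875/0.3 = 5.40.
- Late only: Σ = 0.11; interaction λ = 18.5 × 0.11/0.3 = 6.78.
- For δ = 0.4: change contrast λ = 18.5 × 0.16/0.6 = 4.93; adjusted comparison λ = 18.5 × 0.16/0.51 = 5.80.

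| Profile | Interaction, 4 visits | Change contrast | Baseline-adjusted, post visit |
|---|---|---|---|
| Sustained | 60.8% | 59.2% | 66.2% |
| Fading | 46.4% | 59.2% | 66.2% |
| Late only | 56.6% | 5% | 5% |

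At 46 per group the interaction gives 71.5%, 56.3% and 67.3% for the three profiles. With δ = 0.4 the change contrast gives 68.8% and the adjusted comparison 75.7%.

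**Sensitivity to ρ at 37 per group.** For ρ = 0.5 and 0.8 respectively:
- late divergence only, interaction: 36% and 76%
- fading gain, interaction against adjusted comparison: 29% against 50%, and 65% against 81%
- sustained gain, interaction against change contrast: 39% against 40%, and 80% against 77%

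The sizes move with the assumptions; the pattern does not.

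**Two-visit check.** If time has only the pre and post levels, the interaction F equals the squared t statistic on change scores. In one simulated data set both were 13.024. In that case the protocol's sentence is exactly right.

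**The case against.** The strongest reply is that the analysis section never says four visits enter. It speaks of pre- to post-training change, and elsewhere the protocol uses post-training for one specific visit, distinct from the interim and final follow-up. Read that way, the sentence is correct. This stands as a possibility, and it is why the point is conditional. But the protocol calls all four occasions pre-post measures and describes one ANOVA for the secondary outcomes, so four levels is the more natural reading. The two-level reading leaves the 6- and 12-month assessments without a stated analysis.

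A second reply is that the 3-df test need not be weak. This also stands: for a sustained gain it does about as well as the exact change contrast. The loss is confined to a gain that fades, and the fading profile is an assumption. The protocol does make fading plausible, since it adds booster sessions to help participants retain benefit.

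A third is that the secondary hypothesis in the Background does not tie greater gains in balance and mobility to the immediate post-training visit. That is so, but the interpretive sentence in the analysis section does.

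Three stronger readings are tempting and are not supported:
- A reader might infer that anyone with a missed visit is deleted. That is a property of classical repeated-measures ANOVA with listwise deletion. The protocol does not state it, and handling of missed visits may sit in an analysis plan that is not shown.
- A reader might infer a conflict with intent-to-treat. The inclusion rule is worded for falls-monitoring data only, so there is no rule for the balance measures to contradict.
- A reader might set the interaction in about 74 people (61%) against an adjusted comparison in all 92 (76%). Those samples are unequal. At 37 per group the sustained-gain figures are 61% and 66%, and the difference from the change contrast (59%) comes from baseline adjustment.

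**Conclusion.** The point holds in conditional form. If the four scheduled visits enter the ANOVA, the sentence claims more than the interaction can show. The test is non-directional, and under the assumed late divergence it rejects in 57% of trials with no pre-to-post difference. If the gain fades, its power is 46% against 66% for the adjusted post-training comparison. These percentages rest on 37 per group, ρ = 0.7, compound symmetry and the assumed profiles, none of which the protocol fixes for these outcomes except the approximate number of participants. If only two visits enter, the sentence is correct and the gap is instead the missing statement of how the later values are analysed. Either way the text needs amending. The primary falls analysis and the sample size are untouched.

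**What to change.** Replace the repeated-measures ANOVA for these outcomes with a mixed model for the post-training, 6- and 12-month values, with fixed effects for group, visit, group-by-visit, baseline value, site and balance-failure stratum. Name the baseline-adjusted group contrast at the post-training visit as the test of the pre- to post-training statement, and report the 6- and 12-month contrasts as retention. Reword the interpretive sentence to refer to that contrast.

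The model also keeps participants with partial follow-up. It does not recover anyone without a post-baseline value, which would include people who leave the study before finishing training.

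If ANOVA is retained, the minimum is to state the levels of time, name the pre-to-post contrast, and say how the later visits are analysed.

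The cost is analysis wording only: no new data, visits or participants, and standard software suffices.

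### The inputs listed for the sample size give 37 per group with no overdispersion at all; dispersion and sidedness are not stated, and moderate overdispersion takes power well below 80%

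*Protocol article*

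**What the plan says.** All of this is in the protocol article, section Statistical analysis and sample size. The planned comparison is: "Negative binomial regression will be used to compare fall rates between the two groups". On the sample size: "The target sample size has been estimated using a formula for negative binomial regression described elsewhere". The listed inputs are:

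- control rate: "Assuming a rate of falls in the control group of 1.75 per person per year"
- effect: "a reduction in rate of falling of 46 % in the perturbation training group"
- exposure: "mean follow-up time of 11 months per person"
- error rates: "level of significance (α) of 0.05" and "power (1-β) of 0.8"

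The result is "we estimate that 37 participants per group will be required to show significant effects". It is then raised to 46 per group (92 in total) for 20% withdrawal.

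No dispersion parameter is given, and the alpha is not called one- or two-sided.

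**The concern.** A negative binomial sample size needs one input that a Poisson one does not: the dispersion k, where the variance of a count with mean μ is μ + kμ². It is the only model quantity missing from an otherwise complete numerical list, and the list returns the stated 37 without it.

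Setting k to zero means that everyone in an arm has the same underlying fall rate. The article points the other way. It stratifies on failure frequency in the reactive balance test because this predicts falls in the community (Group allocation and blinding). It expects fall rates to vary with physical activity (Secondary outcomes (follow-up) – activity and participation). It names stroke severity as a prognostic factor (Statistical analysis and sample size).

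If k is appreciably above zero, the primary comparison has a larger chance of missing a true 46% reduction than the planned one in five, and a non-significant result would be judged against a power that the trial did not have.

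**Working it through.** **Inputs.** From Statistical analysis and sample size: control rate r0 = 1.75 per year; rate ratio 1 − 0.46 = 0.54, so r1 = 1.75 × 0.54 = 0.945 per year; mean follow-up t = 11/12 year; alpha 0.05; power 0.80. From Group allocation and blinding: approximately equal allocation. Assumed, because not stated: a two-sided test and a range of k.

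**Formula** (Wald test on the log rate ratio, equal groups):

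n per group = (z_α + z_β)² × [(1/r0 + 1/r1)/t + 2k] / (ln RR)²

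**Reproducing the stated figure.**

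- (1.960 + 0.842)² = 7.849
- (1/1.75 + 1/0.945)/(11/12) = (0.5714 + 1.0582)/0.9167 = 1.778
- (ln 0.54)² = 0.3797
- At k = 0: 7.849 × 1.778 / 0.3797 = 36.75, rounded up to **37**

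This matches. The withdrawal step gives 37/0.8 = 46.25, stated as 46; the rounding is immaterial.

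**Other routes to 37.** Solving for the k at which each variant returns 37:

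| Variance used under the null | Two-sided 0.05 | One-sided 0.05 |
|---|---|---|
| As under the alternative (Wald) | 0.006 | 0.25 |
| Pooled rate | 0.06 | 0.30 |
| Control rate | 0.20 | 0.43 |

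So 37 is compatible with k from zero to about 0.43, depending on two choices that the article does not report.

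**Effect of k, two-sided Wald test.** With V = 1.778 + 2k, power = Φ(√n × 0.6162/√V − 1.960), where 0.6162 = |ln 0.54|.

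| Assumed k | Power, 37 per group | Power, 46 per group | n per group for 80% |
|---|---|---|---|
| 0 | 80% | 88% | 37 |
| 0.1 | 76% | 84% | 41 |
| 0.25 | 70% | 79% | 48 |
| 0.5 | 61% | 71% | 58 |
| 1.0 | 49% | 58% | 79 |
| 1.5 | 40% | 48% | 99 |

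For example, at k = 0.5: 7.849 × 2.778 / 0.3797 = 57.4, so 58. At k = 1.0: 7.849 × 3.778 / 0.3797 = 78.1, so 79.

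Simulation with fitted negative binomial models at 37 per group (600 runs per setting) gave 80%, 60% and 49% for k near 0, 0.5 and 1.0, in line with the formula.

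**Detectable rate ratio at 37 per group, 80% power.** The sample size formula is solved for RR, with r1 = 1.75 × RR changing along with it. This gives about 0.54 at k = 0, 0.45 at k = 0.5 and 0.39 at k = 1.0.

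**Other variants at 37 per group.**

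| Variant | Power, k = 0.5 | Power, k = 1.0 |
|---|---|---|
| Two-sided, control-rate null variance | 69% | 54% |
| One-sided Wald | 73% | 61% |
| One-sided, control-rate null variance | 78% | 66% |

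None reaches 80% at k of 0.5 or more.

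**A sense of scale for k.** k is the squared coefficient of variation of individual rates. Two equal subgroups with rates in the ratio 1 to 3 have mean 2 and variance 1, so k = 1/2² = 0.25. This illustrates the scale; it is not an estimate for this population.

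**The case against.** A reader might infer that 37 can be obtained only with zero dispersion, and so that the authors must have done a Poisson calculation. The documents do not support that. The formula is cited to a source that is not shown, and that source fixes the variance form. The alpha is not called two-sided and the primary hypothesis is directional, so a one-sided test, though less usual, is not excluded. A journal article also condenses, and an input that is not printed was not necessarily zero. This objection stands: the Poisson reading is the simplest match, not a deduction.

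The size of the loss also depends on a k that the article never gives. At k of 0.1 the loss at 37 per group is about four points. The 37-per-group figures are moreover the pessimistic case. The article expects many who leave training to continue falls monitoring, and it analyses everyone with some falls data. With all 46 per group contributing, power is still 79% at k = 0.25. This too stands, and is why both group sizes are shown.

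Finally, the article gives no reason for choosing negative binomial regression; that overdispersion was the reason is an inference. The case for k above zero therefore rests on the risk factors that the article names, not on a motive attributed to it.

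The objection does not remove the point. The article itself fixes the sample size, its inputs and its power, and every variant that reaches 37 needs low dispersion.

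**Conclusion.** The point holds in a conditional form. The listed inputs give 37 per group at zero dispersion under a two-sided Wald test, and no tested variant gives 37 at k above about 0.43. Since the article describes participants whose fall risk differs, the stated 80% is likely optimistic. The shortfall at 37 per group runs from about 4 points at k = 0.1 to about 31 points at k = 1.0. If all 46 per group contribute, power stays above 80% at k = 0.1 and falls to 58% at k = 1.0.

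These sizes rest on an assumed k, a two-sided test and the article's own rates and follow-up. It would go too far to say that the trial is shown to lack 80% power: that would need a dispersion value, and the documents contain none.

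**What to change.** In the sample size paragraph:

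1. State the dispersion assumed, whether the test is one- or two-sided, and which variant of the formula was used. Take k from the data source already used for the 1.75 rate, or from a pooled estimate made during the trial without unblinding.
2. Restate power and the detectable rate ratio for 37 and 46 per group over k from 0 to 1.5.
3. Limit the 80% claim to the dispersion at which it holds.

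The cost is a reworded paragraph and a less favourable stated power. The recruitment target can stay as it is; no extra participants are needed.

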### Safety monitoring

A Safety and Monitoring Committee will be established to ensure that patient safety is maintained by monitoring the trial for possible harmful effects of the intervention (e.g., falls and injuries associated with the intervention). The committee will evaluate the data on adverse events in order to recommend whether the study should continue, be modified, or stopped for safety concerns. The Safety and Monitoring Committee will be an independent multidisciplinary group of 4 members with research and/or clinical experience in rehabilitation post-stroke. Membership will last until the trial is complete. The members will be free of major financial or intellectual conflicts of interest that could prevent them from objectively reviewing the interim data and giving advice. The Safety and Monitoring Committee will meet once prior to the initiation of the trial to discuss and agree on the mandate, and then twice per year until the end of the study to evaluate accrued data on adverse events. Additional meetings may be held if deemed necessary by members of the committee.

## Discussion

Despite the high fall rates experienced by individuals with stroke, and the corresponding increased fear of falling and reduced mobility, there is currently a paucity of research determining how to prevent falls and still maintain independent mobility in this population. While several studies demonstrate the efficacy of exercise for preventing falls in older adults, no study has found that exercise prevents falls among individuals with stroke. It is our view that the capacity for the control of rapid balance reactions is the primary factor that contributes to elevated fall risk and poor balance confidence post-stroke. However, little work has been done to understand the effects of training on reactive balance control. We believe that this novel training paradigm focus of study has the potential to contribute significantly to current knowledge regarding physiotherapy best practices for prevention of falls post-stroke.

